## Abstract

Unipolar depression is a prevalent and disabling condition, often left untreated. In the outpatient setting, general practitioners fail to recognize depression in about 50% of cases mainly due to somatic comorbidities. Given the significant economic, social, and interpersonal impact of depression and its increasing prevalence, there is a need to improve its diagnosis and treatment in outpatient care. Various efforts have been made to isolate individual biological markers for depression to streamline diagnostic and therapeutic approaches. However, the intricate and dynamic interplay between neuroinflammation, metabolic abnormalities, and relevant neurobiological correlates of depression is not yet fully understood. To address this issue, we propose a naturalistic prospective study involving outpatients with unipolar depression, individuals without depression or comorbidities, and healthy controls. In addition to clinical assessments, cardiovascular parameters, metabolic factors, and inflammatory parameters are collected. For analysis we will use conventional statistics as well as machine learning algorithms. We aim to detect relevant participant subgroups by data-driven cluster algorithms and their impact on the subjects’ long-term prognosis. The POKAL-PSY study is a subproject of the research network POKAL (Predictors and Clinical Outcomes in Depressive Disorders; GRK 2621).

## Introduction

Unipolar depression is a common disorder worldwide, with a 12-month prevalence of 4.6% [1]. Unfortunately, only 41% of the affected patients who wanted treatment for their disorder (71%) receive treatment that meets minimum standards [1]. At the same time, depression is one of the most debilitating diseases and imposes a significant challenge to both individuals and society. According to WHO, depression causes 6% of the burden of disease in Europe, if measured in disability-adjusted life years (DALYs) [2, 3]. The worldwide point-prevalence of a depressive disorder was 9.8% (95% CI: 6.7–14.1%) within the years 1994–2003 and has risen to 15.4% (CI: 12.9–18.3%) between the years 2004 and 2014 [4, 5].

Moreover, a patient's psychiatric history was found to be correlated with higher age at graduation on the one hand and unemployment on the other [6]. Early onset of depression was associated with dropout from secondary education [7]. In the context of employment, 5.1% of all days absent from work are attributed to depressive disorders and thus, along with chronic pain disorders, have the greatest negative effect on job attendance [8]. The prognosis is worse the more time passes until diagnosis and adequate therapy is established [9]. Currently, only 55% of depressed patients seeking treatment in primary care settings are detected. Especially, if there are other somatic comorbidities present, mental health disorders are underdiagnosed [10, 11]. While also most psychiatric care is delivered in primary care settings [12], delayed diagnosis and inadequate treatment leads to an increased socioeconomic burden and outcome [13].

Primary care physicians could screen for unipolar depression with the Patient Health Questionnaire 9 (PHQ-9) [14], as it is also recommended by the U.S. preventive task force [15]. Since the PHQ-9 is a self-rating questionnaire, heterogeneous response behavior can’t be avoided, and more extensive diagnostics are needed to determine whether someone has depression [16]. Although diagnostic accuracy is typically higher for clinically experienced psychiatrists, a thorough clinical interview still requires time and experience. Currently, there are no established biological markers that could facilitate and accelerate the diagnostic process for primary care physicians.

A lack of fast, cheap and efficient diagnostic tools in primary care might be a cause for late treatment and detection of unipolar depression. “Unipolar depression” as a clinical phenomenon probably combines numerous biological phenotypes, which significantly complicates the detection of biomarkers using classical statistical methods [17].

### Potential somatic factors and biological predictors

#### Weight gain and metabolism

Considering that primary care physicians typically focus on somatic symptoms, it is important to note that unipolar depression is associated with a range of comorbidities such as increased cardiovascular risk, adiposity, dyslipidemia, as well as high blood pressure and hyperglycemia, resulting in an increased cardiovascular risk [18]. These somatic symptoms might be the main focus of primary care physicians when diagnosing and treating patients, making it even more crucial to consider the possibility of depression and its potential impact on overall health. In fact, the presence of a metabolic syndrome, which is defined as a combination of obesity, low HDL cholesterol, high blood pressure, and elevated blood sugar levels, has been linked to unipolar depression [19]. The metabolic dysregulation in unipolar depression is associated with immunologic changes, which might only affect a clinical subgroup of patients, namely patients with higher childhood trauma scores and rather atypical features of unipolar depression [20, 21]. The link between increased body fat percentage and chronic low-level inflammation [22], childhood trauma, depression, and low physical activity is well documented [22–24]. Increased body weight is associated with decreased well-being, vitality, and quality of life [25]. Weight gain may be followed by the development of metabolic syndrome [26], which increases the risk of cardiovascular disease, autonomous dysregulation [27] and type II diabetes. Patients with unipolar depression have a higher likelihood to suffer from hypercholesterolemia and triglyceridemia compared to their non-affected peers. This association was especially present in women and in patients older than 40 [28]. A lower expression of brain-derived-neurotropic-factor (BDNF), which is associated with mood disorders like unipolar depression, could be observed in mice that were put on a hypercaloric diet [29]. Another hormone that might play an important role in the context of depression and a dysregulated metabolism is Insulin-like Growth Factor—1 (IGF-1). The expression of IGF-1 is influenced by nutrition, BMI and insulin levels, as well as age, sex, and ethnicity. While IGF-1 is mainly known for being a growth hormone that also increases testosterone production [30], evidence further suggests that IGF-1 plays an essential role in dementia, cardiovascular, and metabolic diseases [31, 32]. Elevated IGF-1 levels may increase the risk of developing depression [33, 34], but seems to also mediate the rapid antidepressant effect of ketamine [35, 36].

#### Hypothalamic–pituitary–adrenal-axis

Alterations in the hypothalamic–pituitary–adrenal axis (HPA axis) are involved in neuropsychiatric disorders and have long been a focus of depression research [37]. The dysregulation of the HPA axis is associated with a lack of response to therapy as well as decreased cognitive performance [38]. To date, there is no specific drug targeting the components of the HPA axis that is currently approved and no test that is routinely used in the psychiatric setting to identify patients with HPA-dysregulation [39]. Studies showed that such patients could profit from a normalization of the cortisol rhythms [40].

#### Heart rate variability

In conjunction with the HPA axis, the autonomic nervous system (ANS) forms an extensive and complex network of integrated communication that regulates the body’s physiological homeostasis [41]. The heart rate variability (HRV) is seen as a reflection of the current stress state of the ANS [42, 43]. Chronically reduced HRV indicates autonomic imbalance [44], which is observed in patients suffering from depression or anxiety [45]. Numerous research findings suggest that reduced HRV predicts poor cardiovascular health outcomes, both in heart-healthy populations and in populations with pre-existing cardiovascular disease [46]. The HRV is a trans-diagnostic factor that can be associated with various stress-related conditions and behavioral factors, as well as somatic diseases [47]. While listening to music could increase HRV in stressed participants this effect could not be observed in participants with depression [48], which might be due to reduced resilience, meaning that the autonomous nervous system cannot respond with increased parasympathetic activity [49]. Higher HRV has been associated with psychological flexibility, emotional self-regulation, empathy, and social engagement [50, 51]. HRV could be found to be an important mediator between depression, autonomic dysregulation, and chronic cardiovascular disease [45, 52–54]. A meta-analysis concluded that parasympathetic activity is negatively correlated with inflammation [55], showing again a connection to metabolic disbalances [56]. The complicated dynamic interactions between inflammation and other relevant neurobiological correlates of depression is an indication that a parameter such as the HRV could be an important therapeutic marker for the evaluation of future therapeutic strategies, as well as a diagnostic tool in depressive disorders [57].

#### Inflammation and the dysregulation of the immune system

Excessive or persistent activity of proinflammatory cytokines disrupts numerous neuronal functions, including impairment of neurotransmitter signaling, inhibition of neurotransmitter synthesis as well as neurotransmitter reuptake and release [58, 59]. A bi-directional relationship was postulated, which implies that inflammation modifies the susceptibility to unipolar depression [60]. Chronic inflammation has been postulated as a marker to facilitate the detection of unipolar depression as well as suicidal ideation [61]. Persistent inflammatory processes determined by increased CRP and IL-6 levels are also associated with a lack of response to antidepressants [62–65]. Consistent with this, a randomized controlled trial showed that the addition of an NSAID to psychiatric medication improved treatment response [66]. Also, other anti-inflammatory agents like celecoxib and acetylsalicylic acid curcumin and omega-3 fatty acids are investigated as therapeutic agents [67]. An anti-inflammatory factor is Alpha-1-Antitrypsin (AAT-1), which is a glycoprotein that acts as an inhibitor of various enzymes. In macrophages, AAT-1 inhibits the production of tumor necrosis factor-α and matrix metalloproteinase-12, thus acting as an antagonist of pro-inflammatory markers [68]. AAT-1 was found to be significantly higher in patients suffering from unipolar depression [61]. Consistent with these findings, the severity of an AAT-1 deficiency correlates with an increase of anxiety and depressive symptoms [69].

#### Remaining etiological questions

The aforementioned factors, including inflammation, the dysregulation of the ANS and HPA axis, as well as metabolic implications, form an intricate interplay of various factors as illustrated in Fig. 1. Nevertheless, the true interactions among these aspects remain enigmatic, and a comprehensive concept of the biological underpinnings has yet to be unveiled [17, 22]. Through a comprehensive and collective investigation of these factors, our research strives to shed light on these lingering questions, with the goal of contributing to a broader understanding of unipolar depression.

**Fig. 1 Fig1:**
[figure not shown]
Hypothesized interplay of biological factors in unipolar depression. In this diagram, the interconnectedness of various pathways that are involved in unipolar depression is graphically presented. Negative feedback loops are highlighted with red arrows, while positive feedback is indicated by green arrows. Stress triggers a hormonal cascade, starting with elevated CRH (Corticotropin-Releasing Hormone), which leads to increased ACTH (Adrenocorticotropic Hormone) production, ultimately resulting in the release of Cortisol. High Cortisol levels reduce HRV (Heart Rate Variability) and facilitate the release of inflammatory markers like IL-6 and CRP. In depressed individuals, reduced AAT-1 levels hinder the proper reduction of inflammatory interleukins. Changes in the expression of neurotrophic factors, such as BDNF and IGF-1, have been associated with abnormal neural plasticity. Growth hormone (GH) stimulates the liver to produce IGF-1. IGF-1 also plays a role in insulin homeostasis. Low IGF-1 levels are associated with depression which lead to increased blood sugar levels as well as HbA1c levels

### Study aims and hypotheses

The goal of the POKAL-PSY study is to find relevant risk-factors and predictors determining the severity of unipolar depression in an outpatient setting with a data driven approach. In Addition, easily retrievable parameters should be used to facilitate the diagnostic process in an outpatient setting. To achieve this, we will use clinical parameters as well as a wide array of biological markers such as IGF-1, cortisol, AAT-1, and HRV measurements. We will recruit three cohorts consisting of outpatients with depression at inclusion, patients in primary care without psychiatric disorders, as well as healthy controls with no prior medical history. Moreover, in a cross-sectional analysis, we are aiming to determine whether we can use data-driven algorithms to identify new relevant sub-categories of unipolar depression that are not yet included in current classification systems. In a further step we would investigate the outcomes of each subcategory.

Accordingly, we assume:Functional and structural physiological correlates exist (autonomic nervous system, blood count, inflammatory parameters, fat distribution patterns) that are altered in the presence of depression compared to healthy, or somatically ill but not depressed patients.Physiological and phenotypic differences exist within the overall population of all depressed patients, which influence the outcome and further course of the disease.

## Methods and design

The POKAL-PSY study is a prospective study with three cohorts, where we recruit one cohort with healthy controls (*n* = 50), patients with depression (*n* = 475) and participants without depression (*n* = 425) where participants are monitored for five years. Notably, our emphasis on recruiting individuals with and without depressive symptoms serves to comprehensively investigate the predictors and underlying mechanisms of unipolar depression. The inclusion of patients with somatic comorbidities, who frequently seek medical care, highlights a real-world scenario. For this project, participants will be recruited in a naturalistic setting. Cardiovascular factors (heart rate variability, pulse, blood pressure), metabolic factors (blood lipids, HbA1c, body fat percentage, fasting glucose, IGF-1), as well as inflammatory markers (CRP, AAT-1) will be collected. In addition, the burden of somatic symptoms, lifestyle factors (Eating behavior, chronotype, physical activity), psychopathological characteristics (depression subtype, childhood trauma, anxiety) will be assessed by questionnaires. Depressive relapses will be assessed anamnestically if they occur during the follow-up visits. Patients will be mainly recruited in general practitioner (GP) offices, affiliated with the Bavarian Research Practice Network. Currently, we are recruiting at three different sites. By the end of the recruiting process, our goal is to have recruited from 5 to 6 different sites. We plan to recruit 90% of our study cohort within several GP offices. The inclusion and exclusion criteria are checked in consultation with the treating GPs and in direct patient contact by the study staff and the patients' written consent is obtained. In addition, participants will be recruited at the psychiatric outpatient clinic of the university clinic in Munich. In the context of the POKAL project we cooperate with other research groups and projects by providing validation datasets and support concerning participant recruitment. Specifically, we will cooperate with the MIP3 project (project nr. 21–0357, German Clinical Trials Register number: DRKS00025946). The healthy controls recruited will consist of motivated German citizens. All study personnel were trained to conduct the HRV measurements, as well as the observer ratings. Organizational project management is performed by the Studienzentrum Psychiatrie (SZP) of the LMU Munich. All participants sign a written informed consent form prior to participation. The study was approved by the local ethics committee (project nr. 22–0637, date 14.09.2022) and registered at ClinicalTrials.gov (NCT05547711) and at the German Clinical Trials Register (DRKS00030203). The study presented here is a subproject of the research network POKAL (Predictors and Clinical Outcomes in Depressive Disorders; GRK 2621), which is sponsored by the German Research Foundation (DFG) [70]. Furthermore, all the participants are kindly asked whether they give written consent to participate in the Munich Mental Health Biobank, as well [71]. The POKAL-PSY study is performed in accordance with the regulations of good clinical practice and the declaration of Helsinki [72]. The eligibility criteria can be seen in Table 1.

**Table 1 Tab1:** Overview of the POKAL-PSY study

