### Power calculation

An a priori power analysis was performed to calculate the minimum of needed study participants to conduct a SEM analysis. We assumed a power (1-β) of 0.90 with an effect size of 0.15 and an alpha of 0.05. With these settings a sample size of at least 870 was required to achieve a robust model with 5 latent variables. With estimated screening failures of slightly less than 10% (e.g. development of bipolar disorder in the further course, or with inclusion concealment of a dependence illness) we aim to recruit 950 participants at inclusion. We aim to recruit a sample size of 475 patients with depression and 475 participants without depression. Recruitment in the project presented here will end when the sample size of 950 subjects is reached. Also, this is a sufficient number of participants for machine learning algorithms [106].

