### Planned data analyses

Categorical data will be one-hot-encoded if suitable and summarized with percentages and confidence intervals. For ordinal data the median will be given as well as the interquartile range and for continuous data we calculate the mean as well as the standard deviation and the confidence intervals. Demographic and baseline characteristics in the study arms will be compared with suitable statistical tests. Since multiple comparisons will be performed significant *p*.values will be reported false discovery rate corrected [107]. With the cross-sectional data at inclusion a SEM analysis will be conducted [108]. Furthermore, we will investigate the predictive value of baseline biological parameters for change in depressive symptomatology. In addition, we will design a classification algorithm using all relevant data detecting which participant is depressed. This approach involves the implementation of multiple supervised machine learning algorithms to thoroughly assess their performance. We will evaluate each algorithm during the analysis stage and subsequently select the one that yields the most favorable results. These algorithms may include, but are not limited to, support vector machines, decision trees, and neural networks. Each of these algorithms will be carefully applied and evaluated in the context of our research question. Furthermore, we will use multimodal stacked algorithms to assess the generalizability of different clinical questionnaires and biomarkers separately. To ensure the robustness of our algorithm selection and model performance assessment, we will employ a leave-site-out nested cross-validation approach in each model. This mitigates the risk of overfitting and ensures generalizability. Since the eventual goal of our algorithm is the implementation in a clinical context and to guide general practitioners, we plan to develop a sequential prediction model, which reduces the number of required data modalities and diagnostic uncertainty, as described by Koutsouleris et al. [109]. Sequential stacking models can be used to reduce the data required to produce optimum prediction scores. This method can greatly increase clinical applicability since physicians will be only asked for additional information if needed to achieve satisfactory predictive accuracy [109].

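### Leave-site-out validation over 5 to 6 planned sites can assess, but not ensure, that the algorithm carries over to a new GP practice

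*Protocol article*

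**What the plan says.** Methods and design gives the present state, "Currently, we are recruiting at three different sites", and the target, "By the end of the recruiting process, our goal is to have recruited from 5 to 6 different sites". On where participants come from it says "We plan to recruit 90% of our study cohort within several GP offices", and adds that "participants will be recruited at the psychiatric outpatient clinic of the university clinic in Munich". It does not say whether that clinic counts among the 5 to 6.

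Planned data analyses names the validation scheme, for both algorithm selection and performance assessment: "we will employ a leave-site-out nested cross-validation approach in each model". The next sentence makes the claim at issue: "This mitigates the risk of overfitting and ensures generalizability". The same section gives the purpose: "the eventual goal of our algorithm is the implementation in a clinical context and to guide general practitioners".

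Power calculation derives 870 participants for the structural equation model (SEM), raises this to 950, and then turns to the prediction models: "Also, this is a sufficient number of participants for machine learning algorithms". The number of sites plays no part there.

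The Discussion, under the heading on developing the algorithm, says that validating the model in a follow-up study would be a necessary further step.

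**The concern.** Whether a prediction rule works in a practice that did not help to build it is a question about practices. In leave-site-out validation each site gives one held-out result, so the information on variation between practices grows with the number of sites, not the number of participants. With 5 or 6 sites that information is thin, and no later analysis plan can add to it. Yet the article states as a property of the design that generalizability is ensured, and it judges adequacy for machine learning by participants alone.

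The rest of the plan does not fill the gap. Secondary outcomes proposes testing the cross-sectional algorithm on follow-up data to ensure generalizability. Those are the same participants at later visits, so no new practice is added.

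What is at stake is how far the results can be taken. The tool is meant for general practitioners outside the study, and the design will say little about how far performance in the next practice may fall below the study's figure.

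**Working it through.** **The plan's own figure.** A standard lower-bound formula for SEM, with effect 0.15, power 0.90, two-sided alpha 0.05 and a Šidák adjustment over the 10 pairs of 5 latent variables, gives 869.2, which rounds up to 870. The allowance to reach 950 is 1 − 870/950 = 8.4%, which fits the stated figure of slightly less than 10%. The sample size reproduces. It concerns the SEM and does not bear on validation across sites.

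**Inputs from the article.** N = 950 (Power calculation); k = 5 or 6 sites (Methods and design).

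**Assumptions, not in the article.** Accuracy p = 0.75; equal site sizes; between-site SD of true accuracy τ from 0 to 0.05.

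**Formulas for 95% half-widths.**

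- Participants treated as independent: 1.96 × √(p(1−p)/N)
- Average over sites: t(k−1) × √(τ²/k + p(1−p)/N)
- True accuracy at a new site: t(k−1) × √(τ²(1+1/k) + p(1−p)/N)

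**Numbers.** p(1−p)/N = 0.1875/950 = 0.000197. The participant-level half-width is 1.96 × 0.01405 = 0.0275. The t values are 2.78 (4 df, k = 5) and 2.57 (5 df, k = 6).

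Worked example, new site, k = 6, τ = 0.03: 0.0009 × 1.1667 + 0.000197 = 0.001247; the square root is 0.0353; times 2.57 gives 0.091; and 0.091/0.0275 = 3.3.

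| τ | New site, k=5 | Ratio | New site, k=6 | Ratio | Average over sites, ratio k=5 / k=6 |
|---|---|---|---|---|---|
| 0 | 0.039 | 1.4 | 0.036 | 1.3 | 1.4 / 1.3 |
| 0.01 | 0.049 | 1.8 | 0.046 | 1.7 | 1.5 / 1.4 |
| 0.02 | 0.072 | 2.6 | 0.066 | 2.4 | 1.7 / 1.5 |
| 0.03 | 0.099 | 3.6 | 0.091 | 3.3 | 2.0 / 1.7 |
| 0.05 | 0.157 | 5.7 | 0.143 | 5.2 | 2.7 / 2.3 |

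Ratios are to 0.0275. In simulation (200,000 runs), the participant-level interval covered a new site's true accuracy about 71% of the time at τ = 0.02, 56% at 0.03 and 38% at 0.05.

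**How well the study can learn τ.** Ignoring within-site error, the 95% limits for an SD are about 0.60 to 2.87 times its estimate with 5 sites and 0.62 to 2.45 times with 6. The study could hardly show that variation between practices is small.

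**If the clinic is a fold.** Only 4 or 5 of the 5 to 6 held-out sites would then be GP sites, the setting in which the tool is to be used.

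**The case against.** Four points on the other side have force.

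- **No interval is stated.** A reader might infer that accuracy will be averaged over folds and shown with an interval that ignores site, and so will look several times more certain than it is. The article names no performance measure, pooling rule or interval. Such detail is commonly left to an analysis plan, so its absence is no fault. This stands: the loss of precision can only be put conditionally.
- **The size rests on an assumed SD.** At τ of 0 to 0.01 the new-site ratio is only 1.3 to 1.8. The larger ratios also compare an interval for pooled performance with a prediction interval for one new site, which is wider by construction. For the same quantity, the average over sites, the ratio is 1.7 to 2.0 at τ = 0.03 and 2.3 to 2.7 at 0.05. This stands too. The new-site comparison is still the relevant one for a claim about other practices. It also covers only the classifier of depressed against not depressed; the primary outcome, predicting severity, was not computed.
- **The article tempers itself.** The Discussion calls follow-up validation necessary, and GP use is described as an eventual goal. That weakens any reading that the authors claim readiness for practice. It does not remove the claim in Planned data analyses; the two statements need reconciling.
- **The site count is a goal, and the statement on 950 participants makes no promise about precision across sites.** Both are true. But 5 to 6 is the only target given, and nothing else in the article supports the claim about generalizability.

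Leave-site-out is also a sounder choice than random folds. The objection is to the word *ensures*, not to the method.

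**Conclusion.** The concern holds in a limited form. With the planned 5 to 6 sites, leave-site-out nested cross-validation can assess transfer across 5 to 6 held-out sites. It cannot ensure generalizability, and the article's own call for follow-up validation says as much. This part rests on the text alone.

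The numerical part is conditional on an interval that treats participants as independent, and on an accuracy and between-site SD that the documents do not give. Under accuracy 0.75 and N = 950, such an interval would be too narrow for a new practice by a factor of about 1.3 to 1.8 at SD 0 to 0.01, 3.3 to 3.6 at 0.03 and 5.2 to 5.7 at 0.05. The documents do not support saying that the reported accuracy *will* be overstated in certainty by any particular factor.

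**What to change.** In Planned data analyses:

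1. Replace the claim that the procedure ensures generalizability with a statement that it assesses generalizability across 5 to 6 sites.
2. Report performance for each held-out site.
3. Summarise with a site-level random-effects estimate on a suitable scale, such as the logit, so that limits stay within the possible range. Add a t-based prediction interval for a new practice, and say how imprecise it is with so few sites.
4. State whether the psychiatric outpatient clinic is one of the folds.
5. Make any claim for GP use conditional on the external validation that the Discussion names.

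The lower limit of the prediction interval should not become a binding rule for GP use. With 5 or 6 sites it rests on a very unstable SD, and the calculation assumes that the study sites are exchangeable with future practices.

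The cost is a change of wording, a little more analysis work and a less favourable accuracy statement. Recruitment is expected to run to October 2027, so there is time to make the change.
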